### Outcome Measures

All infants will be assessed by an examiner who is masked to group allocation. A flow diagram of the outcome measures is outlined in Figure 1.

The primary outcome measure is cognitive, language and motor development at two years' corrected age measured using the composite scores from the Bayley Scales of Infant and Toddler Development - 3^rd ^edition (Bayley-III) at 24 months' corrected age[41]. The Bayley-III is a norm referenced developmental scale of cognitive, language and motor development over the first 48 months that has good psychometric properties, and has been used extensively in follow-up of preterm infants.

The secondary outcome measures are as follows

*1. Motor Development *- At 12 and 24 months' corrected age the Neurological Sensory Motor Development Scale (NSMDA)[56] will be used to assess motor development. The NSMDA is a criterion-referenced test of gross and fine motor performance, neurological status, posture, balance and response to sensory input longitudinally. The Alberta Infant Motor scale (AIMs) [57] will be used to assess motor development at 12 months. The AIMS is a norm referenced observational motor assessment used for monitoring the gross motor development of typically-developing infants from birth up to 18 months. Both of these assessments have been selected as they have good psychometric properties, are geared to assessment of motor outcome of infants, are quick and easy to administer with minimal handling, and have relevance to the education of parents about their child's motor maturation.

*2. Infant Behavioral Regulation *- The Infant Toddler Social and Emotional Assessment (ITSEA) [58] will be used at 12 and 24 months. It is a comprehensive adult report measure of social -emotional problems and competencies in 1 to 3 year olds. It consists of 4 broad domains of behavior: dysregulation, externalizing, internalizing and competencies. Parents rate behaviors on a 3 point scale (0 = rarely/not true, 1 = somewhat true/sometime and 3 = Very true/often). It has good internal consistency for the 4 domains, good validity and test-retest reliability.

*3. Primary caregiver mental health *- will be measured with the Hospital Anxiety and Depression Scale (HADS)[59] which has 14 items in total (7 anxiety, 7 depression) at 24 months. Each item is scored with a four-point rating scale scored from 0 to 3, (0 = not at all, 3 = most) giving total scores ranging from 0 to 21 for each subscale and from 0 to 42 for overall distress. A score of 8-10 is suggestive of the presence of the affective state, and scores between 0-7 are within the normal range. It has been validated in a variety of settings and has been found to perform well in assessing the severity of anxiety disorders and depression, not only in primary care patients but also in the general population[60].

*4. Parenting *- The Parenting Stress Index Short Form (PSI-SF)[61] consists of a subset of 36 items drawn from the full version (PSI) organized into three, 12-item subscales: 1) Difficult Child, 2) Parent-Child Dysfunctional Interaction, and 3) Parent Distress and will be used at 24 months. The statements range from 'Strongly Agree' to 'Strongly Disagree'. The questionnaire provides a total stress score and 3 subscale scores, with lower scores indicating less stress. The Short-Form PSI has a correlation of 0.95 with the full length version[61].

*5. Family Burden *- will be assessed using two measures at both 12 and 24 months. The first is the Impact of Family Scale version G (IOF-G)[48] mentioned previously in the methods. The second measure is the Family Assessment Device (FAD) which consists of 60 items rated with a 4-point likert response format (strongly agree to strongly disagree) that assesses six dimensions of family functioning: Problem solving, Communication, Roles, Affective responsiveness, Affective involvement and Behavior control. Additionally, a General Functioning Scale assesses overall health pathology in the family. Both measures have demonstrated satisfactory reliability and validity[62].

*6. Social Support *- the Social Support Questionnaire (SSQ)[63] will be used at 24 months. It contains six items, and each item asks participants to: (a) list the people to whom they can turn and on whom they can rely in given sets of circumstances, and (b) indicate their level of satisfaction with these social supports. An individual's score represents the total level of satisfaction with their social support.

*7. Child-parent interaction *- The structured parent-child play interaction task[64] is an observational task which will be used to assess the quality of parent-child interactions and synchrony at 24 months. It was developed for use with very preterm infants and pre-schoolers, and is an adapted measure from the earlier work by the Dunedin Multidisciplinary Health and Development Research Unit,[65] the National Institute of Child Health and Human Development Study of Early Child Care and Chase-Lansdale et al[66]. The observational instrument consists of four different age-appropriate, problem-solving tasks. The tasks are designed to be challenging for the child and are administered in a set sequence based on the first 3 items' progressive degree of difficulty.

An independent rater will code both the parent and child's behavior for each problem solving task using a 5-point Likert scale. Parent behavior will be assessed using a coding scheme that includes: Positive affect (the overall quality of parent's positive expressions towards their child during each task); Negative affect (the intensity and frequency of the parent's degree of disapproval, anger, and negativism expressed toward the child while working on each task); Supportive presence (sensitivity, warmth and responsiveness to the child as they progress through each task); Facilitates self-regulation (instruction and support provided to the child to assist with successful task completion); and Intrusive/over controlling (Extent to which parent behavior is ill timed, intrusive, and excessively and inappropriately controlling relative to what the child is doing).

The coding scheme used to assess child behavior will include: Positive affect (the overall quality of positive expression/responses of the child during the task); Negative affect (the intensity and frequency of the child's degree of unhappiness, sadness, and hurt expressed during the task); Activity level (how motorically active the child is during each task); Child persistence (extent to which the child is actually problem-oriented on the task); Dependence (extent to which the child displays personal initiative in the situation or, conversely, expects the mother to provide direction and help); and Quality of task transitions (the ability of the child to move from one task to the next).

In addition to the parent and child codes, the dyads' 'interactional synchrony' will be coded on a 5-point Likert scale for each problem solving task. Interactional synchrony assesses the harmony, interconnectedness, responsiveness, reciprocity, engagement, mutual focus and shared affect of the dyad.

*8. Sensory Processing *- The Infant Toddler Sensory Profile Questionnaire[67] which is a parent report measure will be used to evaluate and identify patterns of sensory processing in six sensory systems including: General, Auditory, Visual, Tactile, Vestibular, and Oral Sensory Processing. It is suitable for use with 7 to 36 month olds and will be administered at 12 and 24 months' corrected age. Specific patterns of performance on the Infant/Toddler Sensory Profile Questionnaire have been shown to be indicative of difficulties with sensory processing and performance[67].

### Data Storage

Data will be recorded on paper files and entered electronically into a computerized database and stored securely. A combined database will be created for analysis by merging data from the perinatal and qualitative database, intervention database and outcome assessment data base using the statistical package Stata 10.0. Data will be checked and cleaned again using Stata following merging of files.

### Analysis plan

Analysis will follow standard principles for randomized controlled trials, using simple two-group comparisons performed using all subjects for whom outcome data are available, on an intention-to-treat basis. The primary comparison at 24 months will be based on the Bayley cognitive and motor composite scores, which will be compared between groups using linear regression, controlling for multiple births. Multivariate regression will be used to adjust for potential imbalances in major baseline confounders such as the extent of brain injury (and sociodemographic variables). Secondary analyses will use similar methods to compare the outcomes between groups for the additional motor (NSMDA, AIMs); behavioral (ITSEA), primary caregiver mental health and parent -child interactions measures (VIBES, EAS) at 24 months. For dichotomous outcomes, comparisons will be by chi-squared tests and where continuous data exhibit substantial skewness, non-parametric (Mann-Whitney U test) methods will be used for simple comparisons, and regression analyses performed after appropriate transformation of the outcome.

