### Sample Size Calculations

The primary basis for sample size calculation is the comparison between treatment and control groups on cognitive and motor outcomes at 24 months of corrected age. We consider an important clinical difference to detect would be an improvement of at least 0.4 SD (6 points) in the cognitive and/or the motor scales of the Bayley Scales of Infant and Toddler Development - 3^rd ^edition[41]. With a type-I (alpha) level of 0.05, and 80% power, we will require 100 subjects in each group, i.e., a sample size of 200.

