### Magnetic Resonance Imaging (MRI)

#### Procedure for MRI

Brain MRI will be performed at 38-44 weeks' postmenstrual age at the Royal Children's Hospital. Infants are still eligible for the trial if parents do not consent to MRI. For the MRI, infants will be fed, fitted with earmuffs to minimise noise exposure, then carefully wrapped and placed in a vacuum fixation beanbag (S&S Radiographic Products, Brooklyn, New York) designed to keep the infant still and supported in the scanner[4] All imaging will be obtained without sedation or anaesthesia. Infants will be closely monitored during the MRI scan by electrocardiography and pulse oximetry. MRI will initially be performed using a 1.5 Tesla General Electric Sigma System (General Electrics-Medical Systems, Milwaukee, Wisconsin). When the scanner is upgraded, infants will be scanned using a 3.0 Tesla Siemens Trio (software version 11b and 13b) using a standard 12 channel matrix head coil operating in CP mode.

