### Randomization Process

Infants will be randomly allocated to the intervention and control groups by a computer-generated random sequence, with the treatment allocation concealed in opaque envelopes; only the trial statistician will have access to the code. As parents have the choice to participate in the study without their infant undergoing brain MRI, there will be three strata: 1) nil to mild white matter abnormality, 2) moderate to severe white matter abnormality, or 3) no-MRI group. Secondly, as infants of multiple births need to be randomized to the same group due the family being involved in the intervention, there will also be stratification for multiple births.

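### The primary regression leaves out the white matter stratum used to randomize, which costs a little precision and makes the test conservative

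*Protocol article*

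**What the plan says.** The Randomization Process section of the Protocol article names two stratification factors. For the first, "there will be three strata: 1) nil to mild white matter abnormality, 2) moderate to severe white matter abnormality, or 3) no-MRI group"; the second is multiple birth, because siblings are allocated together. The no-MRI level is needed because, under Procedure for MRI, "Infants are still eligible for the trial if parents do not consent to MRI". The abstract also presents stratification by severity of white matter injury as part of the design.

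The Analysis plan bases the primary comparison on the Bayley cognitive and motor composites, "which will be compared between groups using linear regression, controlling for multiple births". No other covariate is named for that model. The next sentence gives brain injury a different role: "Multivariate regression will be used to adjust for potential imbalances in major baseline confounders such as the extent of brain injury (and sociodemographic variables"). The same section says that comparisons use every subject with outcome data, by intention to treat.

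**The concern.** The article fixes its primary model and names the covariate. That model contains one of the two factors used to randomize and omits the other, with no reason given. This is a mismatch between two stated parts of the design, not a detail left for a later document.

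The role given to brain injury also does not fit the design. Stratification is meant to balance this factor, so correcting imbalance is not the main reason to adjust for it. The reasons are that the standard error should reflect how infants were allocated, and that explained outcome variance should be removed from the residual. Both apply to the primary model. The factor is plausibly prognostic: MRI Qualitative Scoring credits the grading method with good predictive validity. At stake are some precision and a test that runs below its nominal level.

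**Working it through.** **Inputs from the article (Sample Size Calculations).** Alpha and power: "With a type-I (alpha) level of 0.05, and 80% power". Effect: "an improvement of at least 0.4 SD (6 points) in the cognitive and/or the motor scales", so SD = 6/0.4 = 15. Size: "we will require 100 subjects in each group, i.e., a sample size of 200". Sidedness is not stated; two-sided is assumed.

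**Reproducing the planned size.** n per group = 2 × (1.96 + 0.8416)² × (15/6)² = 98.1, rounded up to 99. The t-test version gives 99.1, rounded up to 100. The stated 100 per group reproduces. At n = 100, SE = 15 × √(2/100) = 2.121, and power = Φ(6/2.121 − 1.96) = 80.7%.

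**Assumed input.** R² is the share of Bayley variance explained by the white matter stratum. The article gives no figure, so 5% to 15% is used as the working range, with 2% and 20% as outer checks. For orientation, with two grades R² = p(1 − p)d²/15², where p is the share with moderate to severe abnormality and d the mean difference in points. An assumed p = 0.2 and d = 10 gives 0.2 × 0.8 × 100/225 = 0.071; p = 0.2 and d = 15 gives 0.16.

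**Formulas.** Infants are treated as independent and allocation as balanced within strata.

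- True SE of the group difference: SE_true = 15 × √(1 − R²) × √(2/100).
- SE reported by a model without the stratum: SE_rep = 15 × √(2/100) = 2.121.
- Ratio of interval widths: SE_rep/SE_true = 1/√(1 − R²).
- Actual level without the stratum: 2 × [1 − Φ(1.96 × SE_rep/SE_true)].
- Power without the stratum: Φ((6 − 1.96 × SE_rep)/SE_true).
- Power with the stratum: Φ(6/SE_true − 1.96).

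**Worked case, R² = 10%.** SE_true = 15 × 0.949 × 0.1414 = 2.012. Width ratio = 2.121/2.012 = 1.054. Level = 2 × [1 − Φ(2.066)] = 0.039. Power without the stratum = Φ((6 − 4.158)/2.012) = Φ(0.915) = 82.0%. Power with it = Φ(2.981 − 1.96) = 84.6%.

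| R² (assumed) | Interval too wide by | Actual level | Power without stratum | Power with stratum |
|---|---|---|---|---|
| 2% | 1.0% | 0.048 | 81.0% | 81.5% |
| 5% | 2.6% | 0.044 | 81.4% | 82.7% |
| 10% | 5.4% | 0.039 | 82.0% | 84.6% |
| 15% | 8.5% | 0.034 | 82.7% | 86.6% |
| 20% | 11.8% | 0.028 | 83.4% | 88.5% |

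Over the working range the power cost is 82.7 − 81.4 = 1.3 points to 86.6 − 82.7 = 3.9 points.

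**The case against.** The strongest defence is that adjustment for brain injury is already planned. The only question is then which of two planned models is primary, and a sparse primary model supported by an adjusted one is a recognized approach that introduces no bias. The effect is also small, conservative and dependent on an assumed R²; at 2% the gain is half a point of power. All of this stands. It limits the size of the point but does not explain why one stratification factor is in the primary model and the other is not.

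Three stronger readings are tempting, and the article does not support them.

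- *A reader might infer that infants without MRI are dropped.* The primary model has no brain-injury term and uses all subjects with outcome data, so it loses nobody for lack of a scan. A loss could arise only in the further regression, and only if an MRI grade were entered with complete cases. The article states neither, and the randomization scheme already supplies a no-MRI category.
- *A reader might infer that covariates will be chosen by observed imbalance.* The text speaks of potential imbalances, states no test or trigger, and names brain injury and sociodemographic variables in advance. An open covariate list is normal in an article.
- *A reader might set the adjusted power against the nominal 80%.* That ignores that balanced strata also reduce the true variance behind the unadjusted estimate. On the same basis the comparator is 81.4% to 82.7%, so part of the benefit of stratifying is kept even without adjustment.

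**Conclusion.** The point holds as a modest mismatch between design and analysis: a factor used to randomize is missing from the stated primary model. The consequence is a conservative test and somewhat wide intervals, of the size shown above for an R² of 5% to 15%. The validity of the trial's conclusion is not threatened.

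The figures rest on three assumptions.

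- **R²:** it is assumed and does not come from the article.
- **Balance within strata:** the article does not describe blocking. If balance is weak, the unadjusted test moves back toward its nominal level and its power toward 80.7%; adjustment still gains precision.
- **Independent infants:** siblings are allocated together, and ignoring their correlation would push the reported standard error the other way. The actual level in this trial therefore cannot be stated as a fact from this calculation alone.

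**What to change.** Define the primary model as Bayley composite on treatment, the three-level randomization stratum (nil to mild, moderate to severe, no MRI as its own level) and multiple birth. For siblings whose grades differ, use the stratum under which the family was randomized. This keeps every randomized infant with an outcome in the model, with or without a scan. Any further regression on sociodemographic variables can stay as a supporting analysis.

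The cost is a change of wording and two extra model parameters. The stratum is known for every infant at randomization, so no new data are needed and the sample size does not change.

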### Perinatal data collection

Perinatal data including information on the pregnancy, birth history, and neonatal course (e.g. gestational age, birthweight, gender, multiple birth status, cranial ultrasound findings, proven or suspected necrotizing enterocolitis, maternal antenatal corticosteroid administration, postnatal corticosteroid use and use of oxygen at discharge from hospital) will be collected by the research nurse from medical files and the hospital neonatal database. The primary caregiver will be asked to complete questionnaires when their infant is at term equivalent age, prior to randomization, to obtain the following information:

- *Social Risk *[42]: will be assessed using a 12-point index comprising of six aspects of social status including family structure, education of primary caregiver, occupation of primary income earner, employment status of primary income earner, language spoken at home, and maternal age at birth. Based on the overall risk score, each family will be categorized as lower social risk (0-1) or higher social risk (2+).

- *Edinburgh Postnatal Depression Scale (EPDS) *[43]: will be used to assess primary caregiver depressive symptoms at baseline. It is a widely used 10 item screening tool for postpartum depression. Each item contains a statement such as "I have felt sad or miserable" with four possible responses ranging from "No, not at all" to "Yes, most the time." The primary caregiver is directed to "Choose the answer that comes closest to how you have felt in the past seven days." Each item is scored from 0 to 3 in terms of severity, giving a total score ranging from 0 to 30. The EPDS has demonstrated high reliability and specificity as an indicator of significant depressive symptomatology in new mothers[44]. In this study a cut-off of 12 will be used to indicate depressive symptomatology based upon validation studies[44,45].

- *The Life Stress scale from the Parenting Stress Index *[46]: will be used to examine potentially stressful events within the last 12 months, and whether the respondent thinks that they have a continuing impact. The Life Stress scale is a 19 item scale assessing the number of stressful situational circumstances often beyond the control of a parent (eg. death of a relative, loss of a job). It provides an index of the amount of stress outside the parent-child relationship that the parent is currently experiencing.

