- *The Coping Inventory for Stressful Situations (CISS) *[47]: which is a 48-item inventory will be used to measure three major types of coping styles in an individual, including Task-Oriented (problem-solving), Emotion-Oriented (focuses on consequent emotions, becoming angry/upset), and Avoidance Coping (Distraction and social diversion). Primary caregivers will be asked to rate each item on a five point scale ranging from (1) "not at all" to (5) "very much".

- *Impact on Family Scale (IOF-G) *[48]: will be used to assess the effect of a child's illness on the family system in relation to economic, social, familial, and overall strain. There are 24 items scored on a 4 point Likert scale - (strongly agree to strongly disagree) which measure 4 dimensions of impact upon the family: Financial (economic consequences for the family), Familial/Social (disruption of social interaction), Personal Strain (psychological burden experienced by the primary caregiver and Mastery (coping strategies by the family).

- *The State-Trait Anxiety Inventory (STAI) *[49]: will be used to differentiate between anxiety symptoms with regard to both a current, temporary 'state' of anxiety and a more long standing personality quality 'trait'. It is a 40-item self-report scale divided into two sections, each having 20 questions. Each statement contains a 4 point Likert scale (1= not at all, 4= very much so). Higher scores indicate higher levels of anxiety. For the current study, we will utilized state anxiety to evaluate parents' current anxiety, rather than more stable personality attributes.

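### Caregiver mental health inherits the infant-outcome methods without the caregiver or family being fixed as the unit of analysis, and the pre-randomization caregiver scores are not named as covariates

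*Protocol article*

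**What the plan says.** The Analysis plan starts from an intention-to-treat comparison, "using simple two-group comparisons performed using all subjects for whom outcome data are available". The Bayley cognitive and motor scores come next, "which will be compared between groups using linear regression, controlling for multiple births". A further regression adjusts for possible imbalance in major baseline confounders; brain injury and sociodemographic variables are given as examples. The plan then continues: "Secondary analyses will use similar methods to compare the outcomes between groups". The list that follows includes "primary caregiver mental health and parent -child interactions measures (VIBES, EAS) at 24 months". Dichotomous outcomes get a chi-squared test. Markedly skewed ones get a Mann-Whitney test, plus regression after transformation.

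Under Randomization Process, infants are allocated, siblings of a multiple birth go to the same group, and multiple birth is a stratification factor. Sample Size Calculations asks for 100 subjects per group on the infants' Bayley scores.

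On baseline data, Perinatal data collection says: "The primary caregiver will be asked to complete questionnaires when their infant is at term equivalent age, prior to randomization". These questionnaires include the Edinburgh Postnatal Depression Scale (EPDS), the State-Trait Anxiety Inventory (STAI) and the Impact on Family Scale (IOF-G). Of the STAI it says: "For the current study, we will utilized state anxiety to evaluate parents' current anxiety". Under Outcome Measures, caregiver mental health is the HADS at 24 months. Family burden at 12 and 24 months has two measures: "The first is the Impact of Family Scale version G (IOF-G)[48] mentioned previously in the methods". The other is the Family Assessment Device (FAD). Social support (SSQ) is measured at 24 months.

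**The concern.** Everywhere else in the article, the subject who is recruited, counted and randomized is the infant. HADS, IOF-G, FAD and SSQ describe the caregiver or the family, so a family with twins has one value, not two. A file with one row per infant would hold that value twice, always in the same arm. The standard error would then be too small and the false-positive rate too high.

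Caregiver mental health is one of the trial's stated aims, so an inflated test there would touch a main conclusion. Moving to the correct unit also leaves fewer records, which makes baseline information already in hand more valuable. The plan states the purpose of adjustment as correcting imbalance, and its examples suit infant development better than caregiver distress.

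**Working it through.** **The plan's own figure.** A 0.4 SD difference is 6 points, so SD = 15. With two-sided alpha 0.05 and 80% power, n = 2 × (1.96 + 0.84)² / 0.4² ≈ 98.1, that is 99 per group (99.1 with the t distribution). Power with 100 per group is 0.807. The stated 100 per group reproduces.

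**Duplicated scores: formula.** Let p be the share of infants who are twins, with no higher multiples. The article gives no rate; it says only that multiple births are more common than in the earlier study on which the program is partly based. I assume p = 20%, 30% and 40%. Among N infants there are (1 − p)N singleton families and pN/2 twin families. Copies within a family correlate perfectly, so the design effect is the sum of squared family sizes over the sum of family sizes:

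[(1 − p)N + 4 × pN/2] / N = 1 + p.

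The true type I error of a nominal 5% test that treats rows as independent is 2 × [1 − Φ(1.96 / √(1 + p))].

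**Duplicated scores: simulation.** There were 4,000 runs per value of p, with 100 infants per group and no true effect. Simulation error is about 0.003 to 0.005, from √(0.05 × 0.95 / 4000) and √(0.092 × 0.908 / 4000).

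| Type I error | p = 20% | p = 30% | p = 40% |
|---|---|---|---|
| Formula, score copied per infant | 0.074 | 0.086 | 0.098 |
| t-test, copied | 0.077 | 0.086 | 0.092 |
| Regression with multiple-birth indicator, copied | 0.078 | 0.086 | 0.092 |
| Mann-Whitney, copied | 0.076 | 0.082 | 0.092 |
| One record per caregiver (t-test) | 0.052 | 0.054 | 0.046 |

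The third row shows that the indicator does not help: it shifts the mean for multiples but leaves the copies counted as independent. The chi-squared test was not simulated. It also assumes independent records, so the formula applies to it in the same way.

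**Correct unit and baseline score.** One record per caregiver leaves 100 × (1 − p/2) = 90, 85 or 80 per group. A baseline score with correlation r to the outcome multiplies the residual SD by √(1 − r²). The article gives no r, and its 0.4 SD target was set for the Bayley, so the powers below are illustrations only.

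| Power for 0.4 SD | 90 per group | 85 per group | 80 per group |
|---|---|---|---|
| No baseline score | 0.765 | 0.741 | 0.716 |
| r = 0.3 | 0.803 | 0.780 | 0.756 |
| r = 0.5 | 0.873 | 0.853 | 0.832 |

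Residual variance falls by r²: 16% at r = 0.4 and 36% at r = 0.6. The equivalent gain in families is 1 / (1 − r²), that is 1 / 0.84 = 1.19 and 1 / 0.64 = 1.56.

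**The case against.** The strongest reply is that much of this rests on what a condensed article leaves unsaid. Four readings are tempting and go too far.

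- A reader might infer that caregiver outcomes are compared without adjustment. The text does not support that: the methods carried over include regression controlling for multiple births and regression on baseline confounders.
- A reader might infer that the plan counts a caregiver of twins twice. It never says so. One row per caregiver is a possible reading, and controlling for multiple births could mean a cluster method.
- A reader might infer that the baseline caregiver scores are deliberately left out. The list of confounders is open, and a separate analysis plan may name them.
- A reader might infer that IOF-G, FAD and SSQ are explicitly sent through these methods. The sentence on secondary analyses names caregiver mental health and parent-child interaction, not these scales.

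Two further objections are correct. A comparison without a baseline score is unbiased in a randomized trial and keeps its error rate, so the baseline half concerns precision and chance imbalance, not validity. And only IOF-G is the same instrument at baseline and follow-up; EPDS and STAI are proxies for HADS, taken about two years earlier.

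The part about the unit still stands. The article does not merely leave the method open: it names two tests that assume independent records, in a trial that allocates siblings together and defines no analysis unit other than the subject. The published HADS bands make a dichotomous analysis foreseeable, and skewness is plausible for a symptom scale.

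**Conclusion.** The point holds in a limited form. The plan extends infant-outcome methods to caregiver mental health without fixing the caregiver or family as the unit, and two of its named tests have no means of handling siblings.

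The inflation to about 7-10% is conditional on two things: a caregiver's score being entered once per infant, and 20-40% of infants being twins. With one record per caregiver the error rate returns to about 5%.

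Not naming the baseline caregiver scores is a missed gain rather than an error. Its size depends on a correlation that the article does not give; at 0.4-0.6 it is 16-36% of residual variance. The change is worth making because caregiver mental health is a stated aim and the data are already being collected.

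**What to change.** - Analyse outcomes that describe the caregiver or family (HADS, IOF-G, FAD, SSQ) with one record per family, and say so.
- Analyse child- and dyad-level measures, including the parent-child interaction task, with generalized estimating equations or robust standard errors clustered by family, in place of plain chi-squared and Mann-Whitney tests. For skewed outcomes, the transformed regression already planned can carry the clustered standard errors.
- State whether controlling for multiple births means a covariate, a cluster method or both.
- Prespecify ANCOVA with baseline IOF-G for IOF-G at 12 and 24 months, and with baseline EPDS and STAI-state for HADS. Include the randomization strata in each model.

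This changes analysis wording only; no new data are needed. The small downside is a lower, honest number of units for caregiver outcomes: 80 to 90 per group instead of 100 under the assumed twin shares.
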